
### Sample size

Based on the assumption that a reduction of 25% in VAS scores would be of clinical significance, enrolment of 44 patients in each group is required at the 5% significance level (two-tailed), with a power of 90% to detect differences between the two groups [19]. Considering a 10% possible dropout rate, at least 49 people need to be enrolled in each group.

In this study, we will recruit 60 people for a placebo-controlled, double-blind, crossover trial. After crossover, both the placebo and experimental groups will each be increased to 60 people.

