### Trial design

This is a randomized, double-blind, cross-placebo clinical trial to determine the improvement in rhinitis and asthma symptoms after dust mite exposure reduction. Participants will be randomly divided into 2 groups (group 1 and group 2). From the first day to the 8th week, the patients will apply mite baits or the placebo packages and complete questionnaires three times (V1–V3, V1 = the first day after enrolment; V2 = the fourth week plus or minus 3 days after enrolment; V3 = the eighth week plus or minus 3 days after enrolment). House sampling will be conducted twice (V1 and V3) during this period. After 4 weeks of washout, day 85 marks the beginning of the second phase of treatment.

During this period, the patients will be crossed to accept different interventions for 8 weeks. Questionnaires will be completed three times again (V4–V6, V4 = the twelfth week plus or minus 3 days after enrolment, V5 = the sixteenth week plus or minus 3 days after enrolment, V6 = the twentieth week plus or minus 3 days after enrolment), and house sampling (V4 and V6) will be completed twice again. Finally, we will conduct the questionnaire survey 4 weeks after the end of the intervention (V7, V7 = the twenty-fourth week plus or minus 3 days after enrolment). Throughout the study, the children will receive standard treatments in accordance with asthma and AR guidelines [13]. The efficacy of mite bait in reducing AR and asthma symptoms will be assessed using a visual analogue score (VAS) for rhinitis symptoms, Rhinitis Control Assessment Test (RCAT) score, Rhinoconjunctivitis Quality of Life Questionnaire (RQLQ) score, changes in the level of dust mites, drug usage for asthma and AR, Asthma Control Questionnaire-5 (ACQ-5), and frequencies of acute asthma attacks, emergency visits, and hospitalizations.

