### Interim analyses

At the end of the first phase of the test (V3), an interim analysis of the data from the previous stage will be conducted by the biostatistician of the data monitoring committee, who will primarily analyse the size of the estimated effect in advance and the incidence of adverse events. If there is a lack of treatment effect or the incidence of adverse events is high, early termination of the trial will be considered. These results will be reported back to the trial sponsor, and he or she will decide whether to terminate the experiment or not.

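### The 60-child crossover is justified by what reads as a parallel-group size (44, or 49 with dropout, per group), met only by counting each child twice

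*Protocol article*

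**What the plan says.** The Sample size section takes as its target that "a reduction of 25% in VAS scores would be of clinical significance". It then says that "enrolment of 44 patients in each group is required at the 5% significance level (two-tailed), with a power of 90" percent, the aim being "to detect differences between the two groups". For attrition it adds: "Considering a 10% possible dropout rate, at least 49 people need to be enrolled in each group".

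The next paragraph changes the design: "we will recruit 60 people for a placebo-controlled, double-blind, crossover trial". The two are joined by one sentence: "After crossover, both the placebo and experimental groups will each be increased to 60 people". The section gives no mean VAS, no SD and no within-child correlation.

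Trial design randomises the children to two sequence groups, about 30 each if the split is even. Under Interim analyses, at the end of the first phase (V3), "an interim analysis of the data from the previous stage will be conducted", and early termination may follow if a treatment effect is lacking. The section on statistical methods for primary and secondary outcomes names a two-sample t test, one-way ANOVA and a rank-sum test. It names no paired or crossover method. The Discussion nevertheless presents removal of differences between children as a strength of the design.

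**The concern.** A requirement expressed as patients in each of two groups is a requirement for separate people. Sixty children seen under both treatments give 120 correlated measurements, not 120 patients. Reaching 60 and 60 by counting each child twice ignores what sets the precision of a crossover, namely how much the treatment difference varies within a child. The stated size and power therefore do not belong to the design they are meant to support.

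Two things are at stake. The sponsor is not told what reduction the 60-child crossover can detect. And a reader may carry the 90% over to a comparison of about 30 children with 30, the headcount available at V3, where a decision on stopping may be taken.

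**Working it through.** **Inputs from the Sample size section:** two-sided 5%, power 90%, 44 per group, 25% reduction in VAS, 10% dropout, 60 children.

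**Assumptions made here:** 44 is a two-independent-group figure; sequences are equal (30 and 30); completers number 60 × 0.9 = 54 (27 and 27); within-child correlation ρ is 0, 0.3, 0.5 or 0.7; there is no carry-over.

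**1. The plan's own figures.** 44/0.9 = 48.9, so 49 reproduces. The 44 cannot be derived from the article because no SD is given, so it is solved backwards. With n = 2(1.960 + 1.282)²/d² and n = 44, d = √(2 × 10.51/44) = 0.691; the noncentral t gives d = 0.699. A 25% reduction then corresponds to an SD of 0.25/0.699 = 0.358, about 36% of the mean VAS.

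The figure is sensitive to that SD. By the normal approximation, an SD of 30%, 40% or 50% of the mean would give 31, 54 or 85 per group.

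**2. Crossover contrast.** The period difference within each child is compared between the two sequences. The difference has variance 2·SD²·(1 − ρ), the noncentrality is d√N/√(2(1 − ρ)), and there are N − 2 degrees of freedom. With d = 0.699:

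| ρ | Completers needed in total for 90% | Noncentrality, N = 54 | Power, N = 54 | Reduction detectable with 90% power, N = 54 |
|---|---|---|---|---|
| 0 | 46 | 3.63 | 94.6% | 23% |
| 0.3 | 34 | 4.34 | 98.9% | 19% |
| 0.5 | 24 | 5.14 | 99.9% | 16% |
| 0.7 | 16 | 6.63 | >99.9% | 12% |

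**3. Single-period comparison of group 1 with group 2.** The noncentrality is d√(n/2), with 2n − 2 degrees of freedom.

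- 30 v 30: 0.699 × √15 = 2.71, power 76%. For 90% power, d must be 0.851, a reduction of 0.851 × 35.8% = 30%.
- 27 v 27: 0.699 × √13.5 = 2.57, power 71%. For 90% power, d must be 0.899, a reduction of 0.899 × 35.8% = 32%.

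With 60 children, the two sequence groups cannot both reach 44.

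**The case against.** **The calculation matches the named test.** The article plans a two-sample t test and sorts the data into test and control groups at unblinding, which fits a 60-and-60 reading. This stands to a degree. One might infer that the 90% describes no analysis the trial will do, and the documents do not support that. But an unpaired test on paired data is itself ill-matched to the design. In a simulation with 54 children measured under both treatments and ρ = 0.5, it had 99% power, but its actual type I error was about 0.6% rather than 5%. The agreement shows that the same misfit runs through both sections, so both need changing.

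**The error is conservative.** This stands under the implied SD. A reader might infer that the trial is underpowered, or that no comparison of group 1 with group 2 reaches 90%. Neither follows: the standard crossover test is itself a comparison of the two groups, on period differences, and it exceeds 90% for any ρ of 0 or more. Only single-period comparisons fall short.

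**No power is claimed for V3.** True. Interim analyses describes a look at effect size and adverse events, and names neither a test nor a power. The 71–76% is what a two-sided 5% comparison there would have, not a promise that the plan breaks.

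**The parallel reading is inferred, and the article is condensed.** The source cited for 44 is not available. As 44 pairs, the figure would also give 90% if the SD of the differences were about 51% of the mean. But then neither a requirement in each group nor a doubling to 60 would be needed. The missing SD alone would be no finding, since it may stand in the full protocol. The finding is the stated step from 49 per group to 60 children.

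**Conclusion.** The point holds as a mismatch between the size justification and the design, and the Sample size section is wrong as written. The 44 (49) per group at 90% is neither the requirement nor the power of the 60-child crossover. No division or rounding fails, and enrolment is not shown to be too small.

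If 44 is a parallel-group figure, the crossover needs between 46 completers (ρ = 0) and 16 (ρ = 0.7), and the expected 54 are enough. A period-1 comparison has about 71–76% power for the 25% target and reaches 90% only for reductions of about 30–32%.

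The mismatch itself does not depend on any SD. All the power figures do: they rest on the back-solved SD of 36% of the mean, equal sequences, 10% dropout and no carry-over. A larger true SD would lower all of them, so the reassurance about the crossover is conditional until the SD is stated.

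**What to change.** Keep 60 children and make these text changes:

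- **Sample size:** delete the sentence that raises each group to 60. Restate the calculation for the within-child contrast with 54 completers. Give the assumed mean VAS, SD and within-child correlation, and the power and detectable reduction over correlations of 0.3 to 0.7.
- **Period-1 comparisons:** state that under the same assumptions these have about 71–76% power (to be updated if the assumed SD differs), so that the V3 look is read accordingly.
- **Statistical methods for primary and secondary outcomes:** for the primary VAS comparison, replace the two-sample t test and one-way ANOVA with the analysis that the restated power describes. This is either period differences compared between sequences or a mixed model with treatment, period and child. Without this change the new power figure would again describe a test that is not planned.

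The cost is redrafting two sections and obtaining a defensible SD and correlation. Enrolment, visits and data collection do not change.

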### Recruitment

Recruitment information will be posted on the WeChat official account “Respiratory Angel” of the Department of Respiratory Medicine of the Shanghai Children’s Medical Center.

## Assignment of interventions: allocation

### Sequence generation

Random sequences will be generated using a random number table.

### Concealment mechanism

Random sequences will be successively assigned to the subjects according to the enrolment order.

Odd-numbered subjects will be entered into group 1, and even-numbered subjects will be entered into group 2. Three copies of the generated distribution sequence table will be distributed among the designer, pharmacist, and statistician. Each copy will be sealed in an opaque envelope and kept under lock.

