### Implementation

A special person who is not involved in the subsequent grouping and intervention will be responsible for enrolling the test subjects according to the selection and exclusion criteria. A random sequence will be generated by the statistician. The test designer has decided that odd-numbered subjects will be entered into group 1, and even-numbered subjects will be entered into group 2.

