## Assignment of interventions: blinding

### Who will be blinded

The placebo used in the study looks and smells indistinguishable from mite bait and will be labelled either A or B. The identity of tag A or tag B will be known only to the pharmacists and unknown to the subjects and researchers.

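### The odd/even rule, read literally, is alternation and contradicts the random number table; separately, two trial-wide package codes give the blinding a single point of failure

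*Protocol article*

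**What the plan says.** Four places in the protocol article bear on this point.

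- **Sequence generation:** the method is given in one sentence, "Random sequences will be generated using a random number table".
- **Concealment mechanism:** this section first explains how the sequence is applied: "Random sequences will be successively assigned to the subjects according to the enrolment order". The next sentence gives the rule: "Odd-numbered subjects will be entered into group 1, and even-numbered subjects will be entered into group 2". On custody: "Three copies of the generated distribution sequence table will be distributed among the designer, pharmacist, and statistician", and "Each copy will be sealed in an opaque envelope and kept under lock".
- **Implementation:** the statistician generates a random sequence, and then "The test designer has decided that odd-numbered subjects will be entered into group 1", with even numbers going to group 2. Enrolment is kept separate: "A special person who is not involved in the subsequent grouping and intervention will be responsible for enrolling the test subjects".
- **Who will be blinded:** the packages "will be labelled either A or B. The identity of tag A or tag B will be known only to the pharmacists".

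Intervention description fixes the order. Group 1 receives package A and then B; group 2 receives B and then A. Bait and placebo are said to match in look and smell.

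**The concern.** There are two separate problems.

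**Allocation.** Both statements of the rule attach odd and even to the subject, straight after a sentence about enrolment order. If the number is the enrolment number, nothing random enters the allocation, and whoever controls the order of enrolment controls the group. In a crossover the within-child contrast is largely protected, because every child receives both packages. The interim analysis at V3 is not. At that point each child has had only one package, so a comparison of bait with placebo is a comparison of group 1 with group 2. Under Interim analyses, that look can lead to early termination.

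**Coding.** Two letters serve the whole trial, and each group has a fixed order. Whoever learns what A contains knows the treatment order of every child whose group or label they can see. The primary VAS and the questionnaires are reported by patients or parents, so they are open to bias after unmasking.

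**Working it through.** The plan gives no figure of its own on predictability or balance, so there is none to reproduce. The inputs are 60 children (Sample size), two groups, two package letters and two periods per child (Intervention description).

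**1. What the odd/even rule means**

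| Reading | Method | Next group guessable | Split of 60 |
|---|---|---|---|
| Parity of enrolment number | Alternation | 100% (60 of 60) | exactly 30:30 |
| Parity of random number drawn | Simple randomisation | 50% while the list stays sealed | left to chance |

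On the first reading, the random number table and the sealed copies do nothing. The separate enroller is no safeguard either, because applying a parity rule does not require sight of the list. On the second reading, all the sentences fit together, but none of them says that the number is the random one.

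**2. Balance on the second reading**

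Let X ~ Binomial(60, 0.5).

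- P(X = 30) = C(60,30)/2^60 = 0.103
- P(34/26 or worse) = 2 × P(X ≥ 34) = 0.366
- P(36/24 or worse) = 2 × P(X ≥ 36) = 0.155

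Such imbalance is random in direction. It costs some precision and is not a systematic bias.

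**3. For comparison, permuted blocks**

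In a block of 4 whose size is known, the best guess is right with probability 1/2, 2/3, 2/3 and 1 at the four positions. The mean is (0.5 + 0.667 + 0.667 + 1)/4 = 70.8%. Blocks therefore buy balance at some cost in predictability, which is the reason for varying their size.

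**4. What foreknowledge of the group reveals**

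Group 1 means A first. Whether A is bait is known only to the pharmacists. Foreknowledge of the group therefore becomes foreknowledge of treatment only for someone who also has the key.

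**5. Reach of one disclosure of the key**

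- Trial-wide A/B code: 60 of 60 children, 60 × 2 = 120 child-periods, for anyone who knows the groups or sees the labels.
- Unique code per child and period, with group membership not visible: 1 of 60 children, 2 of 120 child-periods, since learning one period implies the other.

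The two problems compound on the literal reading. The subject number then gives the group, so the enrolment list plus the key is enough to read off all 60 children.

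**The case against.** The strongest defence is that the passage describes the ordinary use of a random number table: each child in turn takes the next random number, and its parity decides the group. Implementation follows the same order, with sequence first and parity mapping second. A generated table, sealed in three locked copies, would be pointless under alternation. This stands as far as it goes. The kinder reading is available, so a reader who infers that allocation was predictable goes beyond the text. What remains is that a rule stated twice says, on its plain words, something other than random allocation.

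It can also be said that nobody without the key can steer a child towards bait first, and that each child receives both packages. Both are correct, and they limit the harm mainly to the V3 comparison.

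A reader might infer that blinding is not secured. The documents do not support that: the packages match in appearance and smell, only the pharmacists hold the key, and the staff member who checks questionnaires does not know the grouping. These measures lower the chance of a break but do not limit its extent. Nor does a parent who learns the content of one bag thereby know other children's groups.

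A reader might also infer that unmasking would bias every outcome. It would not: mattress antigen is measured by ELISA on samples collected by staff.

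Finally, simple randomisation is valid for 60 children, so the lack of blocking is not an error.

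**Conclusion.** The concern holds in two limited parts.

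First, the allocation text contradicts itself or is at best ambiguous. Read literally, the next group is known 100% of the time; on the kinder reading it is 50% guessable, with a 37% chance of a 34/26 split or worse. The documents do not settle which applies, so neither figure can be stated as a fact about the trial. The consequence falls mainly on the between-group V3 interim comparison, and it needs knowledge or a correct guess of the A/B key to become selection by treatment.

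Second, under either reading, one disclosure of the key reaches all 60 children for anyone who knows the groups or sees the labels. This is a single point of failure and not evidence that blinding failed.

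No size of bias in the VAS is claimed. Any such figure would need an assumed shift between periods, which the documents do not give. The sample size is unaffected.

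**What to change.** 1. Replace the subject-number parity rule in Concealment mechanism and Implementation with a statement that the group follows the statistician's concealed random list. The pharmacist should release each child's allocation only after enrolment is recorded. Permuted blocks of varying size are a sensible option if balance is wanted, not a requirement.
2. Replace A and B with a unique code per child and period, and keep group membership out of the records seen by staff who handle packages or questionnaires. Otherwise one broken code together with the group list would still reveal what each group means.
3. Trial status gives a start of 28 July 2019 and an end of 28 June 2020. If allocation is already complete, state which number the parity rule used, give the resulting split, and report any code-break.

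Before packages are prepared, the cost is a revised paragraph, a new list and new labels, with no extra staff. After allocation, it is a clarifying statement in the report.

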### Implementation

A special person who is not involved in the subsequent grouping and intervention will be responsible for enrolling the test subjects according to the selection and exclusion criteria. A random sequence will be generated by the statistician. The test designer has decided that odd-numbered subjects will be entered into group 1, and even-numbered subjects will be entered into group 2.

## Assignment of interventions: blinding

### Who will be blinded

The placebo used in the study looks and smells indistinguishable from mite bait and will be labelled either A or B. The identity of tag A or tag B will be known only to the pharmacists and unknown to the subjects and researchers.

### Procedure for unblinding if needed

When the trial is over, the number of each subject and the treatment plan received need to be checked, and the sealed distribution sequence needs to be decrypted. When unblinding, the intervention measures recorded in the assigned serial number will be checked with the drug delivery record sheet, and the results data will be classified as the test group or the control group for analysis.

## Data collection and management

Baseline data and questions related to the outcome indicators will be designed into questionnaires at https://www.wjx.cn/ and regularly assigned to parents to complete via WeChat. The parents or guardians who will complete the questionnaires are the individuals mainly responsible for the daily life of the child. During the follow-up period, once the questionnaire is completed and submitted, the contents of the questionnaire will not be available for any modifications. In addition, a primary staff member will check whether the parents or guardians completed the questionnaire properly. The staff member will not know the parent grouping or intervention. At the conclusion of the entire experiment, all data will be exported to EXCEL (Microsoft Corporation, Redmond, WA) and analysed using SPSS 20.0 software (SPSS Inc., Chicago, IL).

## Statistical methods

### Statistical methods for primary and secondary outcomes

SPSS 20.0 software will be used to analyse the experimental data. Descriptive statistics will be used for the following data analyses: categorical variables, namely, RCAT scores, ACQ-5 scores, drug usage for asthma and AR, and frequencies of acute asthma attacks, emergency visits, and hospitalizations via frequency tables (i.e. number of evaluable subjects, frequency and percentage for categorical values). The mean ± SD, median, minimum, and maximum will be used as continuous variables, namely, the VAS scores and RQLQ scores. One-way analysis of variance and a two-sample *t* test will be adopted for normally distributed data, and a non-parametric rank-sum test will be adopted for non-normally distributed data. Fisher’s exact and chi-square tests will be used to compare classified data, and *P* < 0.05 will be considered statistically significant.

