### Objectives

The purpose of this study is to evaluate the improvement in rhinitis and asthma symptoms after reduction of dust mite exposure with the acaricide Hestelia Mite Bait through a randomized, double-blind, cross-placebo clinical trial.

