## Interventions

### Explanation for the choice of comparators

We will compare Hestelia Mite Bait containing 0.1% emamectin with a placebo that has a consistent appearance and odour but no acaricidal effect to investigate the change in dust mite exposure and the improvement in asthma and rhinitis symptoms after indoor use of the mite bait.

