### Intervention description

After recruitment (V0), baseline medical characteristics (name, age, sex, diagnosis of asthma and rhinitis and the allergen test report) will be collected. The subjects will be randomly divided into 2 groups. The children randomly assigned to group 1 will be placed with package A for an 8-week intervention. All HDM species reach adulthood within 3 to 4 weeks. Once mature, adult mites have a life expectancy of between 4 and 6 weeks [15]. To avoid an impact of the first intervention on the subsequent intervention, we will establish a 4-week washout period according to the growth cycle of the dust mites. After the 4-week washout period, package B will be placed for an 8-week intervention. In group 2, package B will be placed for an 8-week intervention, followed by a 4-week washout period and then package A will be placed for an 8-week intervention. Each child will undergo a total intervention period of 16 weeks, a washout period of 4 weeks, and a follow-up period of 4 weeks after the end of the second intervention. A flow chart of the study is shown in Fig. 1. At V1, V3, V4, and V6, the staff will collect indoor samples from mattresses using a glass fibre membrane, mite-clearing vacuum cleaner. The components of dust mite antigens in the collected samples will be detected via enzyme-linked immunosorbent assays. Parents will be asked to evaluate the AR and asthma symptom scores and clinical event records at V1–V7 (see the outcome indicators for details), as shown in Table 1.

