#### Secondary outcomes

Change in the RCAT score○ The RCAT demonstrated adequate reliability, validity, and responsiveness and was deemed acceptable and appropriate by the patients. This tool can facilitate detection of AR symptom-control problems, and its brevity supports its usefulness in clinical care. The RCAT consists of 6 items: nasal congestion, sneezing, watery eyes, sleep problems caused by rhinitis, activity avoidance, and rhinitis symptom control. Responses are measured on a 5-point Likert-type scale. RCAT scores range from 6 to 30, with higher scores indicating better rhinitis control [﻿17﻿].Change in the ACQ-5 score○ The ACQ-5 is a questionnaire composed of 5 simple multiple-choice questions that are scored on a scale. The results are obtained by adding the total points and averaging them. It is a rapid assessment tool and plays a significant role in evaluating the extent to which asthma is controlled. Each child will be asked to evaluate the level of asthma control in the previous week. The lower the score is, the better the control level.RQLQ for children with AR [﻿18﻿]○ In this study, children with rhinitis during the previous 1–2 weeks will be evaluated on the basis of their symptoms, psychological status, mental status, social communication, and other aspects of 14 problems caused by rhinitis. The questionnaire is based on a scale according to the following point values: 0 points, normal; 1 point, slight; 2 points, mild; 3 points, serious; and 4 points, very serious. The higher the score is, the more severe the effect of rhinitis on the quality of life.Changes in levels of dust mite antigen in children’s beds○ Three sampling points will be randomly selected for each mattress, and each sampling point will have a range of 30 cm^2^. Each sampling point will be repeatedly vacuumed 10 times using a glass fibre membrane, mite-clearing vacuum cleaner (the bed area will be recorded at the same time). Dust on the glass fibre membrane in the vacuum cleaner will be put into a plastic bag and stored at − 20 °C (killing the dust mites). The samples from each family will be weighed, and then, allergens will be extracted. ELISAs (Indoor Biotechnologies, Charlottesville, VA, USA) will be used to detect the dust mite antigens Der p2 (*Dermatophagoides pteronyssinus*) and Der f2 (*D. farinae*) in the extracted solution.Use of medicines for AR and asthma in children○ The percentages of the children who frequently used anti-asthma drugs for control of rhinitis during the previous 4 weeks were as follows: no use ever, 0%; a total of 1 week of use, 25%; and use every day, 100%. Specific drugs include physiological saline, nasal spray hormone (Mometasone Furoate Aqueous Nasal Spray, Fluticasone Propionate Nasal Spray, Budesonide Nasal Spray, etc.), oral allergy drugs (cetirizine, loratadine, levocetirizine, desloratadine, etc.), Sinupret Drops, montelukast, traditional Chinese medicine (Tongqiao Biyan Granule, Biyuanshu Oral Liquid, Xinqin Granule), nasal allergy medications (levocabastine, azelastine hydrochloride), desensitization treatment (Dermatophagoides Farinae Drops), and inhaled hormones to control asthma (Budesonide Suspension For Inhalation, Seretide, Flixonase, Symbicort Turbuhaler).Number of asthma attacks, emergency visits, frequency of hospitalization

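### Mattress mite antigen is missing from the analysis section's outcome lists, so it falls to general tests that ignore the crossover pairing and give no estimate of the exposure reduction

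*Protocol article*

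**What the plan says.** Protocol article, Objectives: the aim is "to evaluate the improvement in rhinitis and asthma symptoms after reduction of dust mite exposure". Explanation for the choice of comparators: bait is set against placebo "to investigate the change in dust mite exposure and the improvement in asthma and rhinitis symptoms". Exposure is thus one of the two stated targets of the comparison.

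Secondary outcomes includes "Changes in levels of dust mite antigen" in the children's beds, with ELISAs that "will be used to detect the dust mite antigens Der p2" and Der f2. Intervention description fixes the timing: "At V1, V3, V4, and V6, the staff will collect indoor samples from mattresses". Those visits are the start and end of each 8-week phase.

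Statistical methods for primary and secondary outcomes opens with "Descriptive statistics will be used for the following data analyses" and then names outcomes by type. Categorical: RCAT, ACQ-5, drug use, asthma attacks, emergency visits and hospitalisations. Continuous: mean with SD, median, minimum and maximum "will be used as continuous variables, namely, the VAS scores and RQLQ scores". General test rules follow, tied to no named outcome: one-way ANOVA and a two-sample t test for normal data, a rank-sum test for non-normal data, and Fisher's exact and chi-square tests for classified data.

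**The concern.** The section enumerates outcomes and leaves out the one that carries the exposure step. Antigen is then handled by rules that do not fit how it is collected: each child's mattress is sampled under both bait and placebo, yet every test named for continuous data is a test for independent samples.

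Two things are at stake. If a child's two values are positively correlated, an unpaired test uses too large a standard error and loses power. And neither a p-value nor a rank-sum result says by how much the bait lowered antigen, which a reader needs in order to interpret the symptom result in either direction.

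A between-treatment estimate is needed because Strategies to improve adherence to interventions says that staff vacuum-clean the mattress at the four visits, whichever package is in place. A before-to-after fall under bait could come partly from vacuuming. The bait-placebo contrast separates the two.

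**Working it through.** **Step 1: match outcomes to lists.** The protocol has seven outcome groups.

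| Outcome group | Place in the analysis section |
|---|---|
| VAS (primary) | continuous |
| RQLQ | continuous |
| RCAT | categorical |
| ACQ-5 | categorical |
| Drug use | categorical |
| Attacks, emergency visits, hospitalisations | categorical |
| Mite antigen | neither |

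Six of seven are placed; antigen is the only omission.

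**Step 2: which rule then applies.** The lists govern descriptive summaries. The test sentences are general and stand under a heading covering primary and secondary outcomes. Antigen concentration is continuous, so it goes to the t test, ANOVA or rank-sum test. No paired or crossover method is named.

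**Step 3: illustrate the cost.** The plan has no figure of its own to reproduce.

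- n = 60 × (1 − 0.10) = 54 (Sample size section: 60 recruited, 10% dropout).
- Two-sided 5% level (same section).
- Assumed effect: antigen halved, δ = ln 2 = 0.693 on the log scale.
- Assumed SD of the within-child log difference, s: 1.0, 1.5 or 2.0.
- Assumed within-child correlation, ρ: 0.3, 0.5 or 0.7.

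*Paired.* Non-centrality = δ√n / s, with 53 df and critical value 2.006. The 95% CI on the ratio extends by a factor of exp(2.006 × s / √54) each way.

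| s | Non-centrality | Power | CI factor |
|---|---|---|---|
| 1.0 | 5.09 | 0.999 | 1.31 |
| 1.5 | 3.40 | 0.915 | 1.51 |
| 2.0 | 2.55 | 0.706 | 1.73 |

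*Unpaired test on the same log data.* The SD of a single value is σ = s / √(2(1 − ρ)). The test uses SE = σ√(2/n) and, on 106 df, critical value 1.983. The true SE of the mean difference is still s / √n. Power ≈ Φ[(δ − 1.983 × σ√(2/n)) / (s/√n)].

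For s = 1.5, the true SE is 1.5 / √54 = 0.204:

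| ρ | σ | SE used by test | Threshold | Power |
|---|---|---|---|---|
| 0.3 | 1.268 | 0.244 | 0.484 | 0.85 |
| 0.5 | 1.500 | 0.289 | 0.572 | 0.72 |
| 0.7 | 1.936 | 0.373 | 0.739 | 0.41 |

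At ρ = 0.5, s = 1.0 and s = 2.0 give about 0.99 and 0.40, against 0.999 and 0.706 paired. At ρ = 0 the two tests have essentially the same power.

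**The case against.** A reader might infer from the omission that the trial never tests whether exposure fell, and so cannot support its own claim. The documents do not support this. The lists say how outcomes are described, not tested; the general test rules reach any continuous secondary outcome; and no test is tied by name even to the primary VAS. The comparator section states the intent to study change in exposure, and samples will exist at the start and end of both phases. The symptom comparison is randomised and placebo-controlled and needs no antigen result to be valid. All of this stands.

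It is also fair that the plan's summaries include the median, and that a rank test is defensible for skewed data. The protocol shows no antigen distribution, so skewness and non-detects are themselves assumptions. The value given to non-detects, and whether Der p2 and Der f2 are combined, can be left to an analysis plan or fuller protocol.

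One could add that a two-sample t test can be applied properly to within-child phase differences between the two sequences, and the Discussion does speak of removing individual differences. But the article does not say that this is how the test will be used. Its Sample size section counts 60 in each treatment group after crossover, and its unblinding section sorts results into test and control groups for analysis. Both point to an unpaired comparison. Pairing bears on other outcomes too; that does not remove the point for antigen.

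**Conclusion.** The point holds as a fault in the stated method for one important secondary outcome. Antigen is the only outcome left out of the lists, and the rules it defaults to ignore the pairing and name no estimate of the exposure reduction.

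The direction of the loss is firm whenever a child's two values are positively correlated: the unpaired test is then conservative and less powerful. Its size is not firm. Power of 0.92 paired against 0.85 to 0.41 unpaired rests on an assumed SD of 1.5, assumed correlations of 0.3 to 0.7, an assumed halving and 54 completers. The protocol gives no antigen SD or correlation.

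This does not undermine the primary symptom comparison. Nor does it call for a rule that forbids wording the conclusion as improvement after exposure reduction unless the antigen CI excludes 1. A fall in antigen alongside better symptoms would not by itself show that one caused the other, so the wording should be weighed against the estimated ratio.

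**What to change.** In Statistical methods for primary and secondary outcomes:

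- Add mattress mite antigen to the continuous outcomes.
- State that log antigen at the end of each phase (V3 and V6) is compared within child between bait and placebo, allowing for period.
- Report the bait/placebo ratio of geometric means with its 95% CI beside the symptom result, and say that any wording about improvement after exposure reduction will be read against it.

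The V1 and V4 samples remain available to describe change within each phase. Handling of non-detects and of the two antigens can be fixed in the analysis plan before unblinding.

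The cost is a few sentences and one model. The samples are already to be collected and weighed, so no new visits or assays are needed.
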